## 8 STATISTICAL ANALYSES

### 8.1 Sample Size and power considerations

The primary end-point of a 20% reduction in HbA1c has been chosen as the International Diabetes Federation produced in June 2011 new guidelines for the conduct of studies in diabetes using bariatric surgery or devices aiming to produce standardisation allowing comparison between studies. To date there are thus no published large patient group studies using this end-point, so using this new endpoint in a well-designed and conducted study will be of scientific value in itself.

|                                                                                   |                                                                                                  |                                           |                                                             |                                                  |
|-----------------------------------------------------------------------------------|--------------------------------------------------------------------------------------------------|-------------------------------------------|-------------------------------------------------------------|--------------------------------------------------|
| [figure not shown] | Title:
EndoBarrier TM
Gastrointestinal Liner
Diabetes Trial | Protocol No:
Version 5.0 | Sponsor:
Imperial College
London | Date:
5th March 2018 |
|-----------------------------------------------------------------------------------|--------------------------------------------------------------------------------------------------|-------------------------------------------|-------------------------------------------------------------|--------------------------------------------------|

Conservatively, it was estimated that 15% of patients in the control arm will achieve the target but believe this to be an overestimate. The Steno study  is the best quality randomised study (80 patients in each arm) into the effect of best medical therapy published to date and demonstrated over an average 7.8 years significant improvements in HbA1c amongst those having intensive medical therapy from 8.4+/- 1.6 to 7.7+/-1.2, but no change in HbA1c amongst those continuing with standard medical therapy. This study defines the very best that could realistically be achieved in the control arm, but expect there to be very little if any change in this group. The reporting of HbA1c as an outcome measure was not in accordance with the newly defined IDF criteria, but considering the small average reduction achieved in the Steno study, it will be assumed that a target of 15% of patients reaching the endpoint is a conservative estimate. Company data on the small number of patients who have reached a year with the device in place suggest that 40% will achieve this target.

According to our own experience with the device in the commercially sponsored study, up to 30% of patients in the treatment group may have the device removed early. Nevertheless other commercially sponsored (unpublished) studies of this device have achieved lower explant rates ([name] – GI Dynamics). We have therefore diluted the treatment effect from 40% vs. 15% to 35% vs. 15% achieving the target of 20% reduction in HbA1c for treatment arm vs. standard arm. 73 patients per group will give 80% power to detect a significant effect. Adding 10% loss of follow-up increases the sample size to 80 per group.

The dilution was calculated starting from the assumption that 40% of patients with the device will reach the target (this estimate is based on company data based on diabetic patients in the same range of BMI as in the present proposal). If 30% of patients in the treatment group need to remove the device early but remain available for follow-up, in the worst case scenario, the proportion reaching the target is the same as in the control group, bringing the estimate for the treatment group to 32.5%. However most of them will keep the device for some time, having some benefit, so it is plausible to assume that the estimate is higher than 32.5%.

Dividing the main effect 15% vs. 40% in three parts we assume that in the 30% of patients with removal, for 1/3 the same effect will be achieved as in the control group (15% reaching the target), for 1/3 it will be increased (23% reach the target) and for 1/3 more increased (31% reach the target). Overall, this would give an estimate of 35% for the treatment group.

For that reason, 2 arms of 80 patients will be sufficient to ensure demonstration of a significant effect (if one exists) and very conservatively allows for explant rates of up to 30%, a higher, level of benefit in the control arm than is likely to be achieved, and drop-out rates of 10%.

Furthermore the landmark Steno study which in some ways may be considered similar to this study, that had in all likelihood a less effective intervention arm was sufficiently powered with 80 patients in each arm.

More than 80 subjects can be randomised at each study site in the event of patients dropping out post randomisation but prior to treatment start (visit 4). Randomising more patients is possible as the randomisation lists are designed to allow for additional patient recruitment. Also, randomisation

|                                                                                   |                                                                                                  |                                           |                                                             |                                                  |
|-----------------------------------------------------------------------------------|--------------------------------------------------------------------------------------------------|-------------------------------------------|-------------------------------------------------------------|--------------------------------------------------|
| [figure not shown] | Title:
EndoBarrier TM
Gastrointestinal Liner
Diabetes Trial | Protocol No:
Version 5.0 | Sponsor:
Imperial College
London | Date:
5th March 2018 |
|-----------------------------------------------------------------------------------|--------------------------------------------------------------------------------------------------|-------------------------------------------|-------------------------------------------------------------|--------------------------------------------------|

blocks provide sufficient randomisation such that any potential unbalancing would be minor and that final analysis would be unaffected. Any additional randomisation need to be discussed and agreed with the sponsor and the CI. All patients withdrawn post-visit 4, so after treatment start, are part of the initial drop out calculations as per protocol and will not be replaced. At no point, will the total number of patients starting treatment exceed 160 and the final analysis will not be affected.

## 8.2 Data Analysis

Patient characteristics will be summarized. Summaries of continuous variables will be presented as means and standard deviations if normally distributed, and as medians and inter-quartile ranges for skewed data, whilst categorical variables will be presented as frequencies and percentages. The difference between the two study groups in the proportion of patients achieving substantial improvement in the metabolic syndrome both at 12 and 18 months will be analysed using logistic regression adjusting for the stratification variables (BMI groups and sites). Analysis of secondary outcomes will be conducted using standard statistical procedures applicable to categorical or continuous data as appropriate. For missing values we will explore the pattern and the extent of missingness and we will carry out an appropriate form of multiple imputation if required. The analysis will be performed according to the intention to treat principle. All statistical tests will be two-tailed with a 5% significance level.

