## 2 OBJECTIVES AND ENDPOINTS

### 2.1 Primary Objectives

- To compare the EndoBarrier with conventional medical therapy, diet and exercise for obesity related type II diabetes and their effectiveness on metabolic state as defined by the International Diabetes Federation (IDF) with an HbA1c reduced by 20%.

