### 2.4 Primary Endpoints

- Reduction in HbA1c by 20%

|                                                                                   |                                                                             |                                    |                                               |                                            |
|-----------------------------------------------------------------------------------|-----------------------------------------------------------------------------|------------------------------------|-----------------------------------------------|--------------------------------------------|
| [figure not shown] | Title:
EndoBarrier TM
Gastrointestinal Liner
Diabetes Trial | Protocol No:
Version 5.0 | Sponsor:
Imperial College
London | Date:
5 th March 2018 |
|-----------------------------------------------------------------------------------|-----------------------------------------------------------------------------|------------------------------------|-----------------------------------------------|--------------------------------------------|

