## 3 STUDY DESCRIPTION

### 3.1 Design

This study is a randomised controlled trial of the EndoBarrier device compared with standard medical therapy for the management of obese subjects with T2DM. Subjects will be randomised to one of the two treatment arms (see Table 1) of the study via the InForm system (the eCRF database for the study). Over 24 months, the study will be performed at two investigational sites, Imperial College Healthcare NHS Trust in London and University Hospital Southampton NHS Foundation Trust.

Individuals in both study arms will be invited regular medical check-ups including measurement of weight, blood pressure, and blood parameters (HbA1c, cholesterol, triglycerides, fasting blood glucose, insulin), quality of life (EQ-5D) and use of health services, as well as to record any adverse events and medications. Diabetes medication titrations will be conducted by the study diabetologists/endocrinologists in accordance with the guidelines of the American Diabetes Association (see section 5.5.1 for full details). They will also receive routine dietary and exercise counselling as well as telephone counselling from a specialist dietitian. The control arm will be invited for routine follow-up visits to review their standard medical care. Both arms will also be invited to undergo a diversity of tests investigating the mechanism of the EndoBarrier. After 12 months, the EndoBarrier will be removed and both arms will be followed up for a remaining 12 months.

In order to investigate the mechanism of the effect of the EndoBarrier Device, the trial is divided into three sub-groups in each arm who will have the following additional assessments at visits 3, 5, 8 and 10, 14 (see section 5.4 and 5.6 for more detail):

- Sub-group 1 (minimum n=24): functional MRI, eating behaviour, cognitive assessment, and post-meal gut hormones
- Sub-group 2 (minimum n=18): insulin clamps

|                                                                                   |                                                                             |                                    |                                               |                                            |

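### The primary endpoint has no time point, and section 8.2 analyses it at both 12 and 18 months with no success rule, on a sample size that covers one comparison at about one year

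*Protocol*

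**What the plan says.** All references are to the protocol.

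- **Endpoint.** Section 2.4 lists "Reduction in HbA1c by 20" per cent. The objective in section 2.1 speaks of an IDF metabolic state "with an HbA1c reduced by 20" per cent. Neither gives a month or a visit.
- **Analysis.** Section 8.2 compares the "proportion of patients achieving substantial improvement in the metabolic syndrome", and the proportions "both at 12 and 18 months will be analysed using logistic regression adjusting for the stratification variables". Secondary outcomes are dealt with in the next sentence, and no other primary analysis is described.
- **Error rate.** Section 8.2 closes with: "All statistical tests will be two-tailed with a 5% significance level". It gives no ordering of the two times, no split of alpha and no statement of which result decides the trial.
- **Sample size.** Section 8.1 starts from company data in which "patients who have reached a year with the device in place suggest that 40% will achieve this target". Allowing for early removal, it "diluted the treatment effect from 40% vs. 15% to 35% vs. 15% achieving the target of 20% reduction in HbA1c", and arrives at 73 per group for 80% power, or 80 per group with 10% loss.
- **Design.** Section 3.1: "After 12 months, the EndoBarrier will be removed and both arms will be followed up for a remaining 12 months". Month 18 is therefore six months after removal.

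**The concern.** The time point is part of the endpoint's definition, and here two are in play without a rule to join them. They also answer different questions. At 12 months the device has been in for a year, so the comparison measures the effect of treatment. At 18 months it measures what is left after the device has been taken out.

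If the results differ, which is plausible when the device is removed between them, the protocol does not say whether the trial succeeded. The deciding time point could then be picked after the data are seen. Depending on the rule adopted, either the 5% error rate or the 80% power no longer holds.

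**Working it through.** **1. Reproduce the planned size.** Inputs from section 8.1: 35% vs 15%, 80% power. From section 8.2: two-sided 5%. With the pooled two-proportion formula and no continuity correction:

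n = [1.96·√(2·0.25·0.75) + 0.8416·√(0.15·0.85 + 0.35·0.65)]² / 0.20² = 72.4, so 73 per group.

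Power at 73 is Φ[(0.20 − 1.96·0.0717)/0.0697] = Φ(0.854) = 80.3%. The stated 73 is reproduced for one test at one time. The loss step also agrees: 73 × 1.1 = 80.3.

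**2. Trace the planning rates.** The 40% is the one-year, device-in-place figure. With 30% removed early, in equal thirds at 15%, 23% and 31%, the arm rate is 0.7·40 + 0.1·(15 + 23 + 31) = 34.9%, matching the 35%. The control 15% comes from reasoning about a published trial of intensive medical therapy. No 18-month rate is given for either arm.

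**3. If success at either time counts.** Treat the two test statistics as bivariate normal, each tested at two-sided 5%. The protocol gives no correlation between them, so a range is assumed.

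| Assumed correlation | Probability of at least one false positive |
|---|---|
| 0 (upper reference) | 1 − 0.95² = 9.75% |
| 0.3 | 9.5% |
| 0.5 | 9.1% |
| 0.8 | 7.8% |

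**4. If both must succeed.** Type I error is held, but power becomes the bivariate normal probability that both tests are significant, with 73 per group and 35% vs 15% at 12 months.

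| True 18-month rates (assumed) | Correlation 0.3 | 0.5 | 0.8 |
|---|---|---|---|
| 35% vs 15% (full effect kept) | 67% | 69% | 73% |
| 25% vs 15% (half the difference kept) | 29% | 31% | 32% |

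**5. The 18-month test alone, 73 per group, control at 15%.**
- 35%: 80%, as in step 1.
- 30%: Φ[(0.15 − 1.96·0.0691)/0.0680] = Φ(0.214) = 58%.
- 25%: Φ[(0.10 − 1.96·0.0662)/0.0657] = Φ(−0.453) = 33%.

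**6. Which visit is 12 months?** The visit schedule puts V10 at 11.5 months, V11 at 12 months and V13 at 18 months. Table 4 schedules HbA1c at V10 and V13 but not at V11. As scheduled, there is no HbA1c value at the 12-month visit.

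**The case against.** Several points on the other side have force.

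- **Section 8.2 does not name the HbA1c endpoint.** True: its wording is about the metabolic syndrome. That this is the primary analysis is an inference, from its place ahead of the secondary outcomes, from the absence of any other primary analysis, and from section 2.1, which ties the metabolic state to the 20% cut. The inference is strong, but the mismatch of names is itself something to correct.
- **The sentence could mean one sustained-response outcome, reached at both times.** This is the less natural reading but the words allow it. It would give one test and no multiplicity. The planning rates do not describe such an outcome, however, because they start from the proportion responding at about a year.
- **12 months is evidently intended.** The sample size points that way, and the imaging analysis in section 8.2 mentions primary outcomes at one year. That passage concerns exploratory regressions and counts weight loss among those outcomes, so it does not settle the matter.
- **Ordering and alpha allocation can be left to the SAP.** Often so. The primary time point, though, defines the endpoint and underlies the sample size, and the protocol does not leave it open: it states two.

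A reader might infer that the type I error is necessarily above 5%. The text does not support that. Inflation follows only if a win at either time counts, and the protocol states no such rule. A reader might also infer that both planning rates come from patients with a year of device use. Only the undiluted 40% does (step 2).

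**Conclusion.** The concern holds as a defect of definition: the primary time point is not fixed, and no success rule connects the two analyses. The consequence depends on the rule eventually used. With an either-time rule, type I error is about 7.8% to 9.5%. With a both-times rule, power is about 67% to 73% under full persistence of the effect and lower if the effect wanes. Both ranges rest on assumed correlations of 0.3 to 0.8.

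Calling the 18-month test simply underpowered would go further than the document allows. No 18-month effect is specified, so its power is unknown: it is 80% if the full 35% vs 15% persists after removal, and 58% or 33% under the assumed smaller effects. Nor is the planned size for one 12-month comparison in doubt, since that figure reproduces.

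The point should be settled before any outcome comparison is seen, because it decides what the trial can conclude.

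**What to change.** - In sections 2.1, 2.4 and 8.2, name the 20% HbA1c reduction at 12 months as the single primary endpoint, with identical wording in all three, replacing the metabolic-syndrome phrase in section 8.2.
- Name the visit that supplies the value: either V10 (11.5 months), or V11 after Table 4 has been reconciled so that HbA1c is measured there. Section 7.2 recalls patients whose device is removed early at V11 and does not list V10, so the chosen visit must also cover them.
- Make the 18-month comparison a secondary durability endpoint, either tested only if the 12-month result is significant or reported descriptively.

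The cost is a few sentences and, if V11 is chosen, one entry in Table 4. The sample size stays at 80 per arm. The downside is that the 18-month result loses stand-alone primary status.

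Keeping both times as primary would cost more. Splitting alpha to 2.5% each needs 88 per group for 35% vs 15% before loss to follow-up; with 73 per group, power at 2.5% is 71%. It would also require a stated 18-month effect.

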## 2.5 Secondary Endpoints

- HbA1c of less than 6% (or 42 mmol/mol)
- Blood pressure below 135/85 mmHg
- Absolute weight loss greater than 15%
- Reduction in dose/or number of medications
- Frequency of Adverse Events
- Cost of interventions and related health and social care
- QALYs accrued (calculated from area under the EQ-5D curve)
- Incremental cost per QALY within the trial period and over the long-term

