## 4 STUDY POPULATION

### 4.1 Number of subjects to be studied

80 subjects are required per treatment group allowing for drop-outs: a total of 160 patients need to be randomised and start treatment (EndoBarrier device or diet and exercise) at visit 4.

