**Table 4. Summary of blood tests at each study visit**

| Blood test                                             | V1 | V3 | V5 | V6 | V7 | V8 | V9 | V10 | V11 | V12 | V13 | V14 | V15 |
|--------------------------------------------------------|----|----|----|----|----|----|----|-----|-----|-----|-----|-----|-----|
| Haematology (Full blood count)                         | x  | x  | x  | x  | x  | x  | x  | x   | x   | x   | x   | x   | x   |
| Routine Biochemistry (including Urea and Electrolytes) | x  | x  | x  | x  | x  | x  | x  | x   | x   | x   | x   | x   | x   |
| Liver Function test                                    | x  | x  | x  | x  | x  | x  | x  | x   | x   | x   | x   | x   | x   |
| Fasting glucose                                        | x  | x  | x  | x  | x  | x  | x  | x   | x   | x   | x   | x   | x   |
| Creatinine                                             | x  | x  | x  | x  | x  | x  | x  | x   | x   | x   | x   | x   | x   |
| HbA1C                                                  | x  |    | x  |    | x  | x  | x  | x   |     | x   | x   |     | x   |
| Lipids (cholesterol, HDL, LDL, triglycerides)          | x  | x  | x  | x  | x  | x  | x  | x   |     | x   | x   | x   | x   |
| C-Peptide                                              | x  |    |    |    |    |    |    |     |     |     |     |     |     |
| Insulin                                                | x  | x  | x  |    |    | x  |    | x   |     |     |     | x   |     |
| Vitamin D                                              | x  |    |    |    |    | x  |    | x   |     |     |     |     |     |
| Iron studies                                           | x  |    |    |    |    | x  |    | x   |     |     |     |     |     |
| Vitamin B12                                            | x  |    |    |    |    | x  |    | x   |     |     |     |     |     |
| Serum Folate                                           | x  |    |    |    |    | x  |    | x   |     |     |     |     |     |
| Free Thyroxine                                         | x  |    |    |    |    |    |    | x   |     |     |     |     | x   |
| TSH                                                    | x  |    |    |    |    |    |    | x   |     |     |     |     | x   |
| Cortisol (Sub-group 1 only)                            |    | x  |    |    |    | x  |    |     |     |     |     |     |     |

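### The primary logistic model omits baseline HbA1c, and no listed endpoint compares HbA1c between arms on its continuous scale; both can be added using data already collected, for a modest gain in the primary test and a larger one in the secondary analysis.

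*Protocol*

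**What the plan says.** - **Model.** Section 8.2 plans "logistic regression adjusting for the stratification variables (BMI groups and sites". The sentence words its outcome as improvement in the metabolic syndrome at 12 and 18 months. I read it as the primary model because section 2.1 defines the metabolic objective by a 20% HbA1c reduction, and section 8.2 describes no other primary analysis.
- **Endpoints.** The primary endpoint (2.4) is a 20% reduction in HbA1c. The only HbA1c endpoint in section 2.5 is "HbA1c of less than 6% (or 42 mmol/mol", closing the bracket. Both are yes/no.
- **Continuous HbA1c.** In section 8.2 the fall in HbA1c appears as a continuous outcome only in the exploratory within-group regressions for the appetite and brain-reward work.
- **Sampling.** "Table 4. Summary of blood tests at each study visit" shows HbA1c at V1, V5, V7, V8, V9, V10, V12, V13 and V15. It is not measured at V3, or at V11, the 12-month visit.
- **Reason for the binary endpoint.** Section 8.1 says it follows an International Diabetes Federation standard, so that studies can be compared.
- **Sample size.** Section 8.1 says the sponsor "diluted the treatment effect from 40% vs. 15% to 35% vs. 15" per cent, that "73 patients per group will give 80% power to detect a significant effect", and that "Adding 10% loss of follow-up increases the sample size to 80 per group". On testing, section 8.2 says "All statistical tests will be two-tailed with a 5% significance level".

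**The concern.** The chance of meeting either cut-off may depend on where the patient starts. For the 6% threshold the arithmetic is direct. From 7.5%, a patient needs a relative fall of more than 1.5/7.5 = 20%. From 11.0%, the fall must exceed 5.0/11.0 = 45%. For the 20% endpoint the dependence is weaker, because baseline is already the denominator, but it need not be zero. Allocation is stratified by site and BMI group only, so a chance imbalance in baseline HbA1c would go uncorrected in the primary model although the value is on file for every patient.

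The second part concerns scale. The evidence the protocol cites is in mean HbA1c: the Dutch and pilot studies in section 1.2 and the Steno study in section 8.1. Section 8.1 itself says no large published study uses the 20% endpoint. With cut-offs alone, the listed endpoints commit the trial to no between-arm comparison on the scale of that evidence. A moderate glycaemic effect could be missed that the same blood tests would show as a difference in means.

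**Working it through.** **1. The stated sample size.** Inputs from 8.1 and 8.2: 35% vs 15%, two-sided 5%, 80% power, equal arms. With pooled variance and p̄ = 0.25:

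n = [1.960·√(2·0.25·0.75) + 0.842·√(0.35·0.65 + 0.15·0.85)]² / 0.20² = (1.200 + 0.501)² / 0.04 ≈ 72.4, so **73 per arm**.

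This matches the protocol. With 80 per arm and 10% loss, 80 × 0.9 = 72 are evaluable, and power is **79.8%** (80.3% at 73).

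**2. The same effect on a continuous scale.** Assume the responder rates arise from a normal variable shifted between arms. The shift is z(0.85) − z(0.65) = 1.036 − 0.385 = **0.651 SD**.

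- n for 80% power = 2·(1.960 + 0.842)²/0.651² ≈ 37.0, so **38 per arm** (39 with the t distribution).
- Power at 72 per arm = Φ(0.651·√(72/2) − 1.960) = Φ(1.95) = **97.4%**, against 79.8% for the responder comparison.

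**3. The same comparison at the protocol's quoted falls.** Section 1.2 gives falls of 1.3 and 0.8 at six months, read here as percentage points, so the difference is 0.5. The protocol gives no SD of change, so I assume 1.0, 1.2 and 1.6. Baseline is taken as 8.6%, the pilot mean in section 1.2, which makes the 20% cut-off a fall of 0.2 × 8.6 = 1.72 points. Responder rate = 1 − Φ((1.72 − mean fall)/SD).

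| Assumed SD | Responders, device / control | Binary power, 72 per arm | Continuous power, 72 per arm |
|---|---|---|---|
| 1.0 | 33.7% / 17.9% | 59% | 85% |
| 1.2 | 36.3% / 22.2% | 46% | 71% |
| 1.6 | 39.6% / 28.3% | 30% | 47% |

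**4. Adding baseline to the logistic model.** This was simulated with 6,000 trials per row and 72 per arm. The responder rate is 35% vs 15%, and r is the within-arm correlation of baseline HbA1c with relative reduction. The protocol does not give r.

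| r | Site and BMI only | Plus baseline | Gain (points) |
|---|---|---|---|
| 0 | 80.2% | 80.5% | 0.3 |
| 0.2 | 80.5% | 81.2% | 0.7 |
| 0.3 | 79.7% | 81.3% | 1.6 |
| 0.4 | 80.1% | 83.1% | 3.0 |
| 0.5 | 80.6% | 85.5% | 4.9 |
| 0.6 | 79.2% | 87.6% | 8.4 |

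A separate simulation let the fall rise by 0.4, 0.6 or 0.8 points per point of baseline, with residual SD 1.0. Power was 80/78/79% without the covariate and 80/80/82% with it.

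To gauge r, I assumed baseline 8.6 (SD 0.9), follow-up 8.1 (SD 1.0 or 1.2) and a baseline-to-follow-up correlation of 0.3 to 0.7. This gives r from about 0 to 0.5.

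The gain is not a narrower interval on the log odds ratio. At r = 0.5 its standard error rises from 0.43 to 0.48, and power improves because the conditional odds ratio is larger.

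**5. Whether V3 should join the baseline.** Table 2 places randomisation at V2 (−4 weeks) and V3 at −2 weeks ± 7 days. By section 5.2 patients learn their arm at V2, and by section 5.4 they have dietary counselling and a diabetes review at that visit. The liquid diet (5.5.3) starts 7 days before V4, so the V3 window can reach its start. V3 is therefore a post-allocation measurement. Averaging it with V1 would also change little: with an assumed within-person SD of 0.2, 0.3 or 0.4, the simulated control response moves from 13.6 to 13.4%, 14.8 to 14.2%, or 16.2 to 15.2%.

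**The case against.** The strongest objection is that the binary endpoint was chosen deliberately, for comparability under the federation's standard, and that supportive continuous analyses are commonly left to a statistical analysis plan, which is not shown. Section 8.2 also leaves secondary outcomes to methods suited to categorical or continuous data. This stands in part: the primary endpoint should not be replaced, and the unseen plan may already contain the analysis. But the primary model's covariates and the endpoint list are fixed in the protocol, and any such plan would depart from them.

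It is also fair that the covariate alone gains little, since baseline is already built into the 20% endpoint.

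Three stronger readings are tempting, and the document does not support them:

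- **That the primary test should have 97% power.** That figure belongs to a continuous analysis under an assumed normal shift. The primary test stays near 80% after the fix, or a few points above.
- **That leaving V3 blank in Table 4 wastes information already paid for.** No HbA1c is assayed at V3. In an open-label trial, a V3 value would put a measurement taken after disclosure of arm into the denominator of the primary endpoint. Introduced now, it would also define response differently for patients already enrolled.
- **That a single V1 value, also used for eligibility, biases the comparison.** Regression to the mean acts on both randomised arms alike.

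**Conclusion.** The point holds as a modest but nearly free improvement. The protocol fixes a covariate set that leaves out a baseline value already collected, and it lists no between-arm comparison of HbA1c on its continuous scale.

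The covariate is worth about 0 to 4 points of power at low to moderate correlation. The gain of about 8 points needs r near 0.6, above the range found under the spreads assumed here. The firmer reason for adding it is protection against chance imbalance.

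Most of the lost sensitivity comes from the cut-offs, and a continuous secondary analysis recovers it. The 97% against 80% contrast rests on the normal-shift assumption. At the quoted falls the levels depend heavily on the assumed SD, but the continuous analysis has the higher power in every case tried. Nothing here shows that the sample size is wrong or that the primary comparison is biased.

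**What to change.** 1. Keep the 20% reduction as the primary endpoint. In section 8.2, add V1 HbA1c as a continuous covariate beside BMI group and site.
2. Report an adjusted risk difference with the odds ratio, because the adjusted odds ratio is conditional and not directly comparable with an unadjusted one.
3. In section 2.5, add the between-arm difference in mean HbA1c at the end of the treatment period, analysed by ANCOVA adjusted for V1 HbA1c, BMI group and site. Use the V10 value (11.5 months), since Table 4 has no HbA1c at V11.
4. State that V1, the only HbA1c measured before randomisation, is the baseline for all HbA1c analyses. Do not move the V5 assay to V3 or average V1 with V3.

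The cost is amended wording in two sections and a matching entry in the statistical analysis plan. No patient, visit or assay is added. The change should be settled before outcome data are examined by arm.
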